### Design

The study will use three intervention arms and a control arm. The intervention arms will all provide mobile airtime as incentives, but the incentives will be based on different eligibility criteria in the different arms. We will collect ART adherence data continuously for 3 months prior to the intervention, for 24 months after the intervention begins, and for 12 months after the intervention ends for all participants using Wisepill devices. We will acquire routine viral load measures for all participants throughout the study, which will be performed roughly every 12 months as per clinic and Uganda Ministry of Health guidelines. We will also conduct a baseline survey, and then surveys every 6 months for 24 months for all participants. See Fig. 2: SPIRIT figure for a detailed description of the timing of study activities.

**Fig. 2 Fig2:**
[figure not shown]
SPIRIT figure

This study protocol uses the SPIRIT reporting guidelines [37].

### Procedures

#### Intervention components

All participants in the treatment arms will be eligible for a quarterly prize drawing if they meet the goal that corresponds to their treatment assignment, and for an annual prize drawing if they show 90% adherence by the time they reach month 12 (as measured by reaching 90% in the last 3 months of month 12).

#### Quarterly prize drawings

Participants in the three treatment arms will be eligible to enter an in-person or remote prize drawing for a mobile airtime reward every 3 months if they meet their target adherence. In-person prize drawings will be done if the date of the drawing coincides with the participants’ regularly scheduled clinic visits; otherwise, they will be done remotely. Wisepill records adherence remotely, so the study team can monitor adherence without an in-person visit. Remote prize drawings will be conducted automatically by the computer, and the results and airtime reward texted to the participant over the phone.

### Assigned subgoal eligibility

Participants in the assigned subgoals arm will be eligible for the quarterly prize drawing if they reach their assigned subgoal in the respective quarter. The goal will be assigned based on observed baseline adherence, which will be deducted from 90%, and divided by four to get at 4 equal, relatively small, increasing steps. For example, someone with 50% baseline adherence would be asked to reach 60% at month 3, 70% at month 6, 80% at month 9, and 90% at the end of the first intervention year.

### Participatory subgoal eligibility

Participants in the participatory subgoals arm will be eligible for the quarterly prize drawing if they reach the goal they choose for themselves in the respective quarter. The only restrictions are that each goal has to be equal to or higher than the previous one, and that at month 12 90% adherence is reached.

### Fixed goal eligibility

Participants in the fixed goal arm will be eligible for the quarterly prize drawing if they reach 90% adherence in the respective quarter.

Patients scheduled for the in-person prize drawing will also be required to complete a prize drawing survey after they participate in a prize drawing. This survey will measure how feedback given on the achieved versus planned ART adherence influences motivation for future performance and perceived attainability of the next goal. Target, distance, and valence influence attitudes and motivation towards future goals.

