It remains an open question how best to deliver incentives to improve health behaviors. In existing interventions, incentives typically reward individuals for reaching a certain performance goal, commonly a high threshold set uniformly for all individuals, such as a physical activity milestone [19], adherence of 90% [10], or viral suppression [20]. However, people differ in their levels of baseline performance and capacity to improve their performance. Because traditional, high uniform goals do not reward marginal improvements, they consequently reward those with already healthy behaviors. Individuals who are far from such a high threshold must exert great effort to reach it—and yet any marginal improvements they make will not be rewarded, leading to demotivation. For behaviors which require repeated actions such as (daily) adherence, this structure can discourage effort over time, leading to no or only minimal improvement among those not capable of immediately reaching the high goal. In our own studies, adherence improvements were driven by those with already relatively high initial adherence of about 60–80%. Those with adherence below this level did not benefit from our incentive intervention that set the eligibility threshold at 90% mean adherence, and reported that failing to win the incentives caused demotivation [10]. Adolescents and young adults have the lowest levels of self-esteem of any age group [21] and are therefore particularly susceptible to demotivation. Redesigning incentives to enable those (youth) with low baseline adherence to reach their goals is thus of paramount importance.

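### As worded, the prize drawing survey reaches only participants who met their goal, so it cannot record the immediate reaction to a missed goal that its stated purpose calls for

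*Protocol article*

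**What the plan says.** The survey is described at the end of the section on fixed goal eligibility, within the account of the quarterly drawings: "Patients scheduled for the in-person prize drawing will also be required to complete a prize drawing survey after they participate in a prize drawing". Its declared aim is to learn "how feedback given on the achieved versus planned ART adherence influences motivation for future performance", together with how attainable the next goal seems. The text names target, distance and valence as the influences of interest.

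The section on quarterly prize drawings opens a drawing to the three treatment arms "every 3 months if they meet their target adherence". The arm-specific sections repeat the condition. Assigned-subgoal participants are "eligible for the quarterly prize drawing if they reach their assigned subgoal in the respective quarter", participatory-subgoal participants are "eligible for the quarterly prize drawing if they reach the goal they choose for themselves in the respective quarter", and fixed-goal participants need 90% in the quarter. A drawing is in person only when its date coincides with a routine clinic visit. Other drawings are run by computer with the result sent by text, and no survey is described for them.

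The Background explains why reactions to failure matter here: low adherers in the team's earlier incentive study "reported that failing to win the incentives caused demotivation".

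**The concern.** The trial's rationale is that a uniformly high goal discourages people who fall short of it, and that interim goals avoid this. A survey tied to goal feedback is the natural instrument for examining that mechanism, and the informative respondents are those who have just been told they missed. If the survey is given only to people who have just succeeded, the negative side of the feedback is absent by construction.

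A second problem follows. Meeting the goal happens after randomisation and depends on the arm. Respondents in different arms would be differently selected groups, so a descriptive comparison of their motivation would not compare the groups as randomised. It could make the fixed goal look less discouraging than it is.

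**Working it through.** The plan gives no figure for survey completion, so there is nothing to reproduce. The check follows the text.

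1. **Survey to drawing.** The survey comes after participation in an in-person drawing (Fixed goal eligibility).
2. **Drawing to goal.** Participation in a quarterly drawing requires the goal to be met, in every treatment arm (Quarterly prize drawings and the three eligibility sections).
3. **Result.** Anyone surveyed after a quarterly drawing has achieved adherence at or above target. The proportion who missed that quarter's goal is 0% in each treatment arm, without any assumption. Distance from target can vary only upwards, and goal feedback is always favourable.
4. **Other drawings.** The year-1 annual drawing requires 90% adherence, so it adds no route for people who missed that mark. The drawing at the end of the maintenance phase depends on viral suppression instead, but the survey is described with the quarterly drawings.
5. **Second filter.** Remote drawings carry no described survey, which reduces the respondents further.
6. **Selection by arm.** All randomised participants start below 90% (Inclusion criteria). In the protocol's own example, an assigned-subgoal participant at 50% has steps of (90 − 50)/4 = 10 points, so the month-3 goal is 60%. A fixed-goal participant at the same baseline needs 90% at month 3. Qualification is therefore probably rarer in the fixed-goal arm early on.

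**Illustration for one quarter, fixed-goal arm.** Assume that 10% to 30% reach 90%. The document gives no such rate for this population. With 157 per arm (Abstract):

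| Assumed share reaching 90% | Can enter a drawing | Not surveyed that quarter |
|---|---|---|
| 10% | 157 × 0.10 ≈ 16 | 157 − 16 = 141 |
| 30% | 157 × 0.30 ≈ 47 | 157 − 47 = 110 |

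7. **What is still measured.** Follow-up surveys go to all participants at months 6, 12, 18 and 24 and include cognitive and motivational factors (Design; Follow-up surveys). Quarterly assessments up to month 24 fall at months 3, 6, 9, 12, 15, 18, 21 and 24, so four of the eight coincide with a survey that does not depend on meeting the goal. Target attainment is itself an outcome every 3 months, and adherence is recorded continuously.

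**The case against.** The sentence may simply be loose. It speaks of patients scheduled for an in-person drawing, and scheduling turns on the visit date. The stated purpose makes best sense if people who missed the goal are included. The full protocol is not shown and may set out administration rules that include them. This stands as a reason for caution about intent. But the phrase placing the survey after participation narrows the group, and staff applying the text as written would skip those who did not qualify. If everyone was intended, the wording still needs correcting.

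Stronger readings are tempting, and the document does not support them:

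- A reader might infer that demotivated participants go unobserved throughout the trial. They do not: the six-monthly surveys cover everyone, half of the quarterly assessments up to month 24 fall in survey months, and behaviour after a missed goal is visible in the Wisepill data.
- A reader might infer that a trial result is biased. The survey is not a listed outcome, enters no stated model, and is not used for the subgroups, which rest on baseline measures. The selection problem would affect only a comparison of survey responses between arms, and none is announced.
- A reader might take 110 to 141 fixed-goal participants as never surveyed. The figures describe one quarter under an assumed rate, and participants can qualify later. The figure of fewer than 30% at 90% or above in the Background comes from a different sample, aged 15 to 22 and not selected for low adherence, so it does not anchor the range.
- A reader might call demotivation the trial's named main risk. The document presents it as the rationale for subgoals and does not rank risks.

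**Conclusion.** The point holds in limited form. As worded, the prize drawing survey cannot capture the immediate, feedback-linked reaction to a missed quarterly goal, which its own purpose requires. Its respondents are selected after randomisation, probably differently by arm. The 0% share follows from the text alone. The difference in selection between arms is a reasoned expectation, and the one-quarter counts rest on the assumed 10% to 30%.

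What is lost is explanatory evidence about the mechanism, not observation of motivation in general. The primary and secondary outcome analyses are unaffected. The conclusion assumes that the survey sentence is applied as written.

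**What to change.** In the section on fixed goal eligibility, preferably in a paragraph that plainly applies to all three treatment arms, state that the survey is given to every treatment-arm participant whose quarterly goal assessment coincides with a clinic visit. It should come after feedback on achieved adherence, whether or not the target was met. Record the target, the achieved adherence and whether the goal was met.

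If that is not wanted, limit the survey's stated purpose to participants who met their goal, and make no comparison between arms from it.

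The cost is small: a wording change and a few minutes of survey time for participants who missed their goal, at visits already taking place. The downside is slightly more contact in the treatment arms than in control. Phone interviews for assessments that do not fall on a visit are optional. They would widen coverage, but use more resources and increase that contact difference. Recruitment was still under way at the date of this protocol, so at that point an early change could still have captured much of the missing information.

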#### Annual prize drawings

Participants in all three treatment arms will be eligible to enter a larger prize drawing at the end of year 1 if they reach 90% adherence over the course of 12 months.

#### Wisepill procedures

All participants will be given a Wisepill device upon recruitment into the observation period of the study. At the time they receive the device, they will be instructed in how to refill the pill box. The team will only monitor adherence to one antiretroviral as studies show that rates of adherence do not differ significantly across a patient’s medications.

Participants will be asked to use the Wisepill device continuously throughout the study and to notify the study coordinator if their provider changes their regimen during the study (which may be a real possibility, in particular for the youths on prophylaxis). They will be asked to remove only one dose at the time of ingestion and will also be informed that the data recorded will not be shared with clinicians. The team will carefully discuss the restrictions associated with the device with the patient and solutions to potential concerns that are acceptable to both the patient and the project will be generated. We will review the instructions and restrictions with the participant at each successive clinic visit.

The 3-month period will also allow individuals to incorporate the device into their daily life and to test and troubleshoot its use prior to beginning the intervention. During this time, we will monitor their adherence. Participants who are unable to use the device consistently will be excluded from the study after careful discussion of the reason for the low observed adherence with the patient (to avoid excluding participants with truly low adherence that is not related to an inability or unwillingness to use the Wisepill device). We will also exclude participants who have adherence above 90% during this period to target the intervention at those with low Wisepill-measured adherence (as those over 90% adherence have little room and/or need for improvement).

### Intervention modifications

Participants will be discontinued from the study if they experience serious adverse events related to the intervention. Participants will also be discontinued from the study at their own request, if they are not in a position to adhere to study protocols which include the use of Wisepill devices to monitor their medication intake.

### Study timeline

The SPIRIT figure above shows the study timeline.

#### Recruitment

During recruitment for the observation phase, the client will be given a Wisepill device. During this recruitment visit, the study coordinator will consent the participant and explain the reason for and conditions of using the Wisepill device. Participants will be compensated 10,000 USh for their time.

As dates of the next appointment are readily available from the electronic medical records system, the clinic system will allow us to print out weekly lists of eligible clients together with the date they are expected at the clinic, and the date they are scheduled for their next viral load test.

We will consent and enroll 4–6 clients per day (some clients may refuse participation, though this has been rare in our previous studies) during the 9- to 12-month recruitment period. Based on the large clinic population and our previous experience, we expect to easily recruit the 1256 clients within a 12-month period but allow for sufficient extra time to accommodate any delays due to public holidays and other reasons for clinic closures or other delays.

### Baseline survey and randomization

When the client returns for their next scheduled clinic visit after the observation period (after about 3 months) and is eligible based on their observed adherence, we will conduct the baseline survey, reveal treatment assignment to either the control or one of the three intervention groups, and begin the intervention. In scheduling these return visits, we will aim to schedule them to coincide with a scheduled clinic visit so that participants do not have to come to the clinic for the sole purpose of study activities. However, participants with next scheduled visits longer than 3 months will be messaged or called to come back at the 3-month mark.

The baseline survey contains the following information:Demographics and socioeconomic status, including age, gender, education, relationship status, employment type and status, income, housing, economic shocks, and household composition;HIV status and clinic visits, e.g., respondents will be asked whether they have disclosed their status to members they live with and the number of those who have HIV/AIDS, their primary caregiver, the person that ensures they take their ART medication, and their clinic visit habits and expenses;Adherence self-efficacy, i.e., reasons for non-adherence or failure to seek care (we will use an 11-item modification developed by the ACTG, that asks participants to indicate whether listed items were reasons for their not taking medication in the previous month or seeking care, such as “when the drugs make you feel bad,” or “when your daily routine is interrupted,” or “lacked resources).Participants’ subjective experiences related to taking medications [38] using the Intrinsic Motivation Inventory. The survey will also collect information related to behavioral economics biases such as present bias or risk preferences.

### Follow-up surveys

Follow-up surveys will be conducted at month 6, 12, 18, and 24 post baseline. These assessments will allow us to collect several data points for each participant on mediators or moderators that we believe may be influenced by the intervention (e.g., cognitive and motivational factors). Participants will be compensated 30,000 UGX for their time every time they complete a survey questionnaire.

### Retention

To promote participant retention and complete follow-up, the study has aligned its activities with the participants’ clinic visit dates. By doing this, the study aims to ensure that participants are not only coming to the clinic for study-related activities but also for their routine clinical visits. This approach is expected to reduce the burden on participants, minimize missed appointments, and increase compliance with the study protocol. Participants who discontinue the study will return their Wisepill devices and we will not be collecting outcomes data.

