### Outcomes

#### Primary outcome

Outcome 1: Mean adherence to ART (Time Frame: adherence over a 12-month period continuously tracked remotely): Wisepill devices monitor the date and time of all device openings to retrieve ART medication, allowing ART adherence to be tracked continuously on the Wisepill server. Mean adherence will be coded as the number of ART doses taken / number of doses prescribed, with adherence being capped at 100% each day to avoid multiple openings on a given day artificially inflating mean adherence.

Outcome 2: The fraction of clients with adherence of 90% or more (Time Frame: continuously tracked remotely).

Outcome 3: Probability of reaching adherence target (Time Frame: tracked every 3 months corresponding to routine prize drawing opportunities). Probability that participants in the treatment groups reach their assigned target (T1), self-selected target (T2), or high fixed target of 90% (T3).

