#### Secondary outcomes

Outcome 1: Fraction of clients with treatment interruptions of more than 48 h (Time Frame: Continuously tracked remotely).

Outcome 2: Suppressed viral load (viral load ≤ 200 copies/ML) among participants (Time Frame: At baseline and month 24): Viral load will be chart abstracted from clinic data. They are typically done once a year as part of routine clinical care.

Outcome 3: Retention in Care, chart abstracted from clinic data. First, we will use the binary definition of retention from the Health Resources and Services Administration HIV/AIDS Bureau as at least 2 clinic visits separated by 90 days in the previous 12 months. Second, we will use the more detailed measure outlined by Lee et al. [12] to create a variable that categorizes clients as having different levels of retention in care that provides more granular information about retention. We will define a client as fully retained in care if they attended all scheduled appointments over the previous 12 months (usually 4 or 5 total appointments). We will then create three different levels of care disengagement: missed one appointment but not more than 6 months without a visit, missed 2 appointments or 6–9 months without a visit, and missed 3 or more appointments or 9–12 months without a visit.

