### Data analysis

Our primary analyses will be intention-to-treat analyses, with secondary analyses involving study completers only.

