### Handling missing data and attrition

Missing data have been a minor issue in our previous studies with the same study population and outcomes. Attrition has been well under 10% per year. However, when subjects drop out, we will fit multiple logistic regression models to assess whether this dropout is random. If it is not, we will construct “nonresponse” weights using logistic regression that correct for dropout by assigning weights to continuing subjects that are inversely proportional to the predicted probability of the subjects’ continuing to the time period in question. Analyses will incorporate design effects from this weighting in the calculation of standard errors and tests of significance. In addition, we will present sensitivity tests regarding changes in outcomes when excluding those with missing observations to give a fully transparent picture of the data.

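### Outcome collection stops when a participant leaves the study, although viral load and retention in care could still be read from clinic charts; this conflicts with the stated viral load coverage and the intention-to-treat analysis.

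*Protocol article*

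**What the plan says.** All references are to the protocol article.

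- **Retention:** "Participants who discontinue the study will return their Wisepill devices and we will not be collecting outcomes data". No outcome is exempted.
- **Secondary outcomes:** two of the three listed come from clinic records. For suppression, "Viral load will be chart abstracted from clinic data". The other is given as "Outcome 3: Retention in Care, chart abstracted from clinic data". The remaining one, treatment interruptions, is tracked remotely.
- **Design:** "We will acquire routine viral load measures for all participants throughout the study".
- **Data analysis:** "Our primary analyses will be intention-to-treat analyses, with secondary analyses involving study completers only".
- **Primary outcome:** adherence comes from the device: "Wisepill devices monitor the date and time of all device openings to retrieve ART medication".
- **Intervention modifications:** participants leave the study after an intervention-related serious adverse event, or at their own request "if they are not in a position to adhere to study protocols which include the use of Wisepill devices".
- **Handling missing data and attrition:** when people drop out, "we will fit multiple logistic regression models to assess whether this dropout is random". Inverse-probability weights for those who continue follow only if dropout is found not to be random. The named sensitivity analysis leaves out people with missing observations.

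**The concern.** Leaving this study means giving up the device and the study activities. It does not mean leaving the clinic. For many leavers the clinic will go on recording visits and viral loads, and the Retention rule gives those records up.

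The loss may be informative. Leaving is linked to difficulty with study procedures, including device use. Device openings earn prize eligibility in the three incentive arms and nothing in the control arm. Exit related to adherence, and different by arm, is therefore plausible, although the article gives no data on it. Study activities are also aligned with clinic visits, so study exit and disengagement from care are probably correlated.

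At stake is whether the suppression and retention results describe everyone randomised or only those who stayed. In the second case the primary analysis of these outcomes moves close to the completer analysis that the plan calls secondary.

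**Working it through.** **1. The passages side by side.** Design promises viral loads for all participants throughout. Data analysis makes intention-to-treat primary. Retention ends all outcome collection at discontinuation. For outcomes read from charts, the third statement cannot be followed together with the first two. For Wisepill adherence there is no such choice, because nothing can be recorded once the device is returned.

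**2. The plan's own figure.** Sampling and participants inflates 560 (140 per arm) for 6% attrition a year over two years: 560 × 1.06² = 629.2, reported as 629 and reduced to 628 (157 per arm). This reproduces. Sample size and power assumes 10% a year, so both rates are used below.

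**3. Ceiling on people without chart outcomes.** Treat all assumed attrition as discontinuation. Number lost = 628 × [1 − (1 − d)^t], with d the yearly rate and t in years.

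| Yearly rate | Month 12 | Month 24 |
|---|---|---|
| 6% | 628 × 0.06 = 38 | 628 × (1 − 0.94²) = 73 (11.6%) |
| 10% | 628 × 0.10 = 63 | 628 × (1 − 0.90²) = 119 (19.0%) |

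**4. Effect on viral suppression.** If true suppression is p, a share L leaves, and leavers are suppressed at rate q, the stayers show (p − L·q)/(1 − L). Take p = 0.70 in both arms (the control value in Sample size and power), so there is no true effect. Assume 19% loss in controls and 10% in an incentive arm. The arm difference and q are assumptions.

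- q = 0.5: incentive (0.70 − 0.050)/0.90 = 72.2%; control (0.70 − 0.095)/0.81 = 74.7%; difference −2.5 percentage points (pp).
- q = 0.3: incentive (0.70 − 0.030)/0.90 = 74.4%; control (0.70 − 0.057)/0.81 = 79.4%; difference −4.9 pp.
- Equal loss and equal q: difference 0, but the level rises. With 11.6% loss and q = 0.5 both arms show 72.6%; with 19% loss and q = 0.3 both show 79.4%.
- q = 0.70: no distortion at all.

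These are unweighted. The plan's stated detectable difference for suppression is about 10 pp at month 12 and 11 pp at month 24.

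**5. Effect on retention in care.** Same formula, with an assumed true retention of 85%. If half of the leavers stay in care, stayers show (0.85 − 0.1164 × 0.5)/0.8836 = 89.6% at 11.6% loss, and (0.85 − 0.19 × 0.5)/0.81 = 93.2% at 19% loss. If leavers are retained at 85%, there is no distortion.

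**6. Can the dropout test be relied on as a trigger?** The article gives no decision criterion. Assume a two-sided 0.05 comparison of two arms of 157, normal approximation: power = Φ(|p1 − p2|/SE − 1.96), with SE = √[(p1(1 − p1) + p2(1 − p2))/157].

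- 19% versus 10%: SE = √(0.2439/157) = 0.0394; 0.09/0.0394 − 1.96 = 0.32; power about 63%.
- 15% versus 10%: SE = √(0.2175/157) = 0.0372; 0.05/0.0372 − 1.96 = −0.62; power about 27%.

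A dropout difference that matters would often go undetected, and the weights would then not be used.

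**The case against.** The strongest reply has five parts.

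- **Withdrawal by choice.** Intervention modifications reads most naturally as participants leaving at their own request, not as staff removing poor device users. Some may also refuse record access, and their data could not be used. How many is unknown. This stands, and it limits how much is recoverable.
- **Run-in.** Wisepill procedures uses the three months before randomisation to resolve device problems and exclude people who cannot use it consistently. Low use after randomisation is recorded as low adherence and is not dropout in itself. This stands, and it makes large device-driven loss less likely.
- **Weights are planned.** This stands in part. They are conditional, use only measured predictors, and rest on the stayers' data. The named sensitivity analysis excludes the same people again, so it cannot probe the problem.
- **The numbers are a ceiling and a scenario.** This stands. Attrition is not defined as discontinuation, the 10% rate is called conservative, and nothing in the article supports a difference in loss between arms.
- **Design may already intend full viral load coverage.** Possibly. Then the two sections still have to be reconciled, and retention in care has no equivalent statement.

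A reader might go further and infer that the retention outcome is conditioned on itself, or cannot be estimated in those who leave. The article does not support that. Someone who misses clinic visits without leaving the study can still be abstracted and counted as disengaged, and someone who leaves the study may stay in care. Nor does the article say that data gathered before discontinuation are discarded.

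**Conclusion.** The concern holds for the chart-based secondary outcomes. The Retention rule contradicts the Design and Data analysis sections, and it gives up recoverable viral load and clinic-visit data from a group selected on an event probably related to adherence and care engagement.

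The number affected at month 24 is at most 73 (6% a year) to 119 (10% a year) of 628, if all attrition is discontinuation. The between-arm error in suppression ranges from zero, with equal loss and similar leavers, to 2.5 to 4.9 pp in the assumed unequal scenario. There it runs against the incentive arm and, at its largest, is a little under half of the detectable difference that the plan states.

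For the three primary outcomes, all based on Wisepill adherence, missing data after device return are unavoidable. A reader might take the rule to invalidate the primary intention-to-treat analysis, but the article does not support that. What can be improved there is how the missing part is handled. This should be corrected, but it does not undermine the trial.

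**What to change.** 1. **Reconcile Retention, Design and Data analysis.** State that returning the device or leaving study activities does not end chart abstraction. Abstract viral load and clinic visits for every randomised participant over the planned follow-up, unless consent for record access is withdrawn, and analyse them in the arm assigned.
2. **Wisepill adherence.** State that data up to discontinuation are kept. Apply the inverse-probability weights already described without a preliminary test of whether dropout is random.
3. **Sensitivity analysis.** Replace or supplement the analysis that excludes people with missing observations with one that assigns pessimistic adherence after discontinuation.

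The cost is a little more abstraction, of a kind already planned for the other participants, and one more analysis. Recruitment is under way, so the consent wording may need checking for people already enrolled. The sample size does not change.
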